## Abstract

**Introduction::**

Cerebral palsy is the most common motor disability of childhood. Spastic cerebral palsy accounts for 60% to 70% of cases. Research has shown that acupuncture can improve the quality of life of children with cerebral palsy, but the mechanism of action remains unclear. This study aims to determine the effectiveness of acupuncture for treatment of children with spastic cerebral palsy and to assess the value of multimodal magnetic resonance imaging (MRI) and ambulatory electroencephalogram (EEG) for evaluation of treatment effect.

**Patients consent::**

Obtained.

**Ethics approval::**

The central independent ethics committee of Jiangsu Province Hospital of Traditional Chinese Medicine approved the protocol (2017NL-115-02).

**Safety considerations::**

Routine blood tests and liver and kidney function tests will be conducted to exclude patients with severe heart, liver, or kidney diseases. The same examinations will be performed again at the end of the study to detect any possible side effects. Possible acupuncture-related adverse events (e.g., fainting, needle stick injury, local infection, subcutaneous hematoma, and low-grade fever) will be documented. Serious adverse events will be reported to the principal investigator immediately. All unexpected and unintended responses, even those not necessarily related to the acupuncture intervention, will be documented as adverse events.

**Case dropout management::**

Participants have a right to withdraw from the study at any time if they feel uncomfortable upon receiving the treatments or being diagnosed with serious complications or diseases. They will then be referred to the preferred department for further treatment and management. If cases of dropout, the researcher need to contact the participant to reason the problem out, collect and record all the necessary assessments on the last visit as well as the date of last visit. All data available until the date of withdrawal will be stored for further statistical analysis.

**Discussion::**

This research is being conducted to assess the value of acupuncture as an intervention for rehabilitation of children with spastic cerebral palsy and also to evaluate the usefulness of multimodal MRI and ambulatory EEG for identifying changes in brain function.

**Trial registration::**

This trial is registered with Chinese Clinical Trials Register, ChiCTR 1900024546 (registered 15 July 2019; retrospective registration, http://www.chictr.org.cn/showproj.aspx?proj=35763).

Strengths and limitations of this studyMRI and EEG can provide a more precise assessment of the treatment effect.The sample size of this study is not large.This study is confined to only 1 subtype of cerebral palsy, i.e., spastic cerebral palsy.MRI is most likely to be rejected by parents due to the prolonged duration of the examination.The results of MRI might vary or be unclear because children are unlikely to cooperate during the examination.

## Introduction

1

Cerebral palsy (CP) comprises a group of permanent disorders of movement and posture caused by nonprogressive disturbances that occurred in the fetal or infant brain. The motor disorders of CP are often accompanied by disturbances of sensation, perception, cognition, communication, and behavior, and sometimes by epilepsy and secondary musculoskeletal problems.^[1]^ Currently, CP affects 1% to 5% infants worldwide, and the prevalence is reported to be increasing.^[2]^ In China, a survey of 6 provinces found a prevalence of 1.2% to 2.7%.^[3]^ According to 1 estimate there are a total of 400 to 500 million children with CP in China, 42% to 45% of whom are physically disabled, and around 3 to 4 million new cases are being added each year.^[4]^

Spastic CP, which is seen in 60% to 70% of cases,^[5]^ results from damage to areas of the brain that control reflex actions; affected children therefore present with increased muscle tone, decreased range of motion of the joints, disturbances of posture, and activity limitation. Treatment includes neurological rehabilitation (Bobath concept and Vojta method); basic rehabilitation (cerebral palsy rehabilitation and core stabilizing training); physical therapies (functional electrical stimulation, biofeedback therapy, and transcranial magnetic stimulation); assistive devices; occupational therapy; conductive education; surgery, psychological rehabilitation, and nursing care. While these treatments may reduce spasticity and improve motor function over the short term, the effects are not long lasting.

There is increasing interest in the use of traditional Chinese medicine, especially acupuncture, in CP, and acupuncture was even included in the 2015 China Guidelines Protocol in Cerebral Palsy Rehabilitation.^[6]^ Some studies have shown that acupuncture in combination with standardized rehabilitation can greatly improve motor function in children with CP and improve quality of life,^[7,8]^ but the mechanism of action, duration of efficacy, and individual differences in efficacy remains to be clarified.

This clinical trial aims to determine the effectiveness of acupuncture in spastic CP.

## Methods

2

### Study design

2.1

Randomized controlled trial comparing 2 treatments: “Tonifying Kidney and Invigorating Brain” acupuncture plus standard rehabilitation versus standard rehabilitation alone for treatment of children with spastic CP.

### Setting

2.2

The study is currently underway in 2 different hospitals, Jiangsu Province Hospital of Chinese Medicine and Nanjing State Hospital of Pediatric.

### Patient and Public Involvement

2.3

No patient involved.

### Intended sample size

2.4

The following formula was used to calculate the intended sample size considering an average efficiency of 92% and 63% for the treatment and the control groups, respectively, α = 0.05, and β = 0.2: 

Thus, the estimated sample size for each group is 30. However, assuming a shedding rate of 20%, the sample size would increase by another 20%. Thus, the sample size intended for each group is 36, with a total sample size of 72.

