### Participants

2.5

A total of 72 children with CP will be recruited (36 from each of the 2 hospitals) and randomly assigned to the treatment group or the control group in a ratio of 1:1 (Fig. 1).

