### Informed consent

2.6

Trial objectives, characteristics, probable benefits and risks, alternative treatments available, and the participants rights and obligations, as stated in the Declaration of Helsinki, will be explained to the parents of the patients before obtaining their written consent. A representative from the research team approached families and described the study. Families were given adequate time to reflect on the information, had any questions answered and gave free and voluntary consent. Parents or legal guardians then provided written informed consent. If new ethical issues emerge during the course of the trial, the informed consent format will be revised and resubmitted to the Ethics Committee for approval; then, the participants consent will be requested again. In case any patient withdraws from the study, all data available till the date of withdrawal will be included in the final analysis.

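### The 20% drop-out allowance is applied as 30 × 1.2 = 36 per group, which covers a loss of only 16.7%: a minor arithmetic error

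*Protocol article*

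**What the plan says.** All the figures are in the protocol article, under Intended sample size (2.4). The calculation is made "considering an average efficiency of 92% and 63% for the treatment and the control groups, respectively", with "α = 0.05, and β = 0.2". The result is that "the estimated sample size for each group is 30". Drop-out is then allowed for in one step: "assuming a shedding rate of 20%, the sample size would increase by another 20"%. The conclusion is that "the sample size intended for each group is 36, with a total sample size of 72".

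The Participants section (2.5) repeats the total of 72, "randomly assigned to the treatment group or the control group in a ratio of 1:1". No section gives another inflation rule or a lower expected loss. On children who leave, the Informed consent section (2.6) says that "all data available till the date of withdrawal will be included in the final analysis".

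**The concern.** The plan names a required number (30 per group) and an expected loss (20%), and presents 36 per group as the size that reconciles them. It does not. The six added children are 20% of 30, but the loss is taken from the 36 who are randomised, and 20% of 36 is 7.2. At the plan's own loss rate, each group ends below its own target.

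What is at stake is the accuracy of a stated design property. A report that repeats the section would say that the trial was sized to absorb 20% loss, when it was sized to absorb about one child in six. The effect on power is small, but it runs in the unfavourable direction.

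**Working it through.** **Inputs** (Intended sample size, 2.4; allocation from Participants, 2.5): response 92% v 63%; α = 0.05; β = 0.2; 30 per group before drop-out; loss d = 20%; 36 per group after drop-out; 1:1 allocation. *Assumption:* a two-sided test, because sidedness is not stated.

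**1. The base figure of 30.** The formula does not appear in the extracted text, so standard ones were tried. The arcsine formula is n = (z₀.₉₇₅ + z₀.₈₀)² / [2(asin√p₁ − asin√p₂)²].

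- asin√0.92 = 1.2840 and asin√0.63 = 0.9169; the difference is 0.3671.
- (1.960 + 0.842)² = 7.849.
- n = 7.849 / (2 × 0.1348) = 29.1, which rounds up to 30.

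The plan's 30 is reproduced. The unpooled normal approximation, 7.849 × (0.92 × 0.08 + 0.63 × 0.37)/0.29², gives 28.6, so 29.

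**2. The plan's inflation step.** 30 × (1 + 0.20) = 36 per group, and 2 × 36 = 72. Both stated figures are reproduced.

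**3. What remains after the stated loss.** 36 × (1 − 0.20) = 28.8 per group, or 57.6 in total, against 30 and 60. The shortfall is 1.2 children per group.

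**4. The loss that 36 does cover.** 1 − 30/36 = 16.7%.

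**5. The size that would cover 20%.** 30/(1 − 0.20) = 37.5, so 38 per group and 76 in total. Check: 38 × 0.80 = 30.4, whereas 37 × 0.80 = 29.6 is still short.

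**6. Effect on power** (92% v 63%, two-sided 0.05):

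| Method | 30 per group | 29 | 28.8 | 28 |
|---|---|---|---|---|
| Arcsine | 81.2% | 79.8% | 79.6% | 78.4% |
| Unpooled normal approximation | 81.8% | 80.5% | 80.2% | 79.1% |
| Chi-square test, exact enumeration | 80.3% | 78.6% | – | 77.0% |

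For example, arcsine power at 28.8 is Φ(√57.6 × 0.3671 − 1.960) = Φ(0.826) = 79.6%. Going from 30 to 28.8 costs about 1.6 points by either approximation. By exact enumeration, the cost is 1.7 points at 29 children and 3.3 at 28.

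**7. Sidedness.** With a one-sided 0.05 test, the arcsine requirement falls to 22.9 per group, so 28.8 would clear 80%.

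**The case against.** **Children who leave still contribute.** Data up to withdrawal enter the final analysis, and the case dropout section (2.10) has assessments collected at the last visit. Outcomes are taken at 3 and 6 months, so a child lost during follow-up may still have a 3-month assessment. This stands in part: 28.8 need not be the count at every time point. It does not repair the 6-month count, because data up to withdrawal cannot supply an assessment that was never made. The dropout criteria listed under Randomization (2.9) include children who do not continue follow-up or cannot cooperate with assessments.

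**The shortfall is small.** It is 1.2 children per group, and correcting the statement changes neither enrolment nor analysis. This stands, and it is why the point is minor.

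**A reader might infer that the trial misses its 80% power.** The document does not establish this. The formula cannot be seen and sidedness is not stated. Of the two-sided results at 28.8, one lies just under 80% and one just over.

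**A reader might also infer that the base of 30 is wrong, or that power is far below 80%,** by choosing a more conservative formula or test. The arcsine formula gives 30, and exact chi-square power at 30 is 80.3%. Where another method already falls short at 30, that gap comes from the choice of method and not from the drop-out step. Nor does the Statistical methods section (2.14) name any test of proportions; it lists t tests and the Wilcoxon rank sum test. The power figures here therefore describe the plan's own sizing assumptions and no named analysis.

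**Conclusion.** The concern holds as a minor arithmetic error. The size part is certain and needs only the plan's printed numbers: with 20% loss, 36 per group leaves 28.8 and not 30; 36 covers at most 16.7%; and 20% would need 38 per group.

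The power part is conditional. For 92% v 63% at two-sided 0.05, the loss is roughly 2 points, or about 3 by exact enumeration if only 28 children remain. Whether this takes power below 80% depends on the unseen formula and the unstated sidedness. The conclusion assumes that the 20% is a loss from those randomised and that children who drop out lack the later outcome.

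**What to change.** Keep 72 and replace the drop-out sentence in Intended sample size with wording such as:

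> Enrolling 36 per group retains 30 if loss does not exceed 16.7%. At 20% loss, about 28 to 29 per group remain, with power slightly lower than planned.

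Drop the claim that 36 allows for 20% loss. There is no need to print a revised power percentage, since it would depend on the formula and on a comparison of proportions that the Statistical methods section does not name. The sentence should not combine 72 with a 20% allowance computed as n/(1 − d), because at 20% that rule gives 76.

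The cost is one corrected sentence and a slightly less favourable statement of power. The Setting section (2.2) says that the trial has already begun, and no further children are needed for this correction.

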### Participants

2.5

A total of 72 children with CP will be recruited (36 from each of the 2 hospitals) and randomly assigned to the treatment group or the control group in a ratio of 1:1 (Fig. 1).

**Figure 1 F1:**
[figure not shown]
Participant flow diagram.

Diagnosis will be according to 2015 China Guidelines Protocol in CP Rehabilitation:^[6]^

Main criteria:

1.Disorder of the central nervous system with persistent motor dysfunctionality2.Abnormality of the development of movement and posture3.Abnormality of muscle tone and muscle power4.Abnormality in muscle reflex

Secondary criteria:

1.Evidence related to etiology of cerebral palsy.2.Present of magnetic resonance imaging (MRI) report

According to the guidelines there are 6 types of CP: spastic quadriplegia, spastic diplegia, spastic hemiplegia, ataxic CP, mixed CP, and dyskinetic CP. Only children with spastic forms of CP will be considered for inclusion in this study.

*Inclusion criteria*:

1.diagnosis of spastic CP,2.age between 6 months and 7 years,3.willingness to participate in the study (parents sign the inform consent form on behalf of their children).

*Exclusion criteria*:

1.severe form of spastic CP or2.presence of a serious comorbidity (e.g., congenital heart disease, hydrocephalus, increased intracranial pressure, psychiatric or psychological disorders, liver or kidney dysfunction, or chronic infectious disease).

### Informed consent

2.6

Trial objectives, characteristics, probable benefits and risks, alternative treatments available, and the participants rights and obligations, as stated in the Declaration of Helsinki, will be explained to the parents of the patients before obtaining their written consent. A representative from the research team approached families and described the study. Families were given adequate time to reflect on the information, had any questions answered and gave free and voluntary consent. Parents or legal guardians then provided written informed consent. If new ethical issues emerge during the course of the trial, the informed consent format will be revised and resubmitted to the Ethics Committee for approval; then, the participants consent will be requested again. In case any patient withdraws from the study, all data available till the date of withdrawal will be included in the final analysis.

### Confidentiality

2.7

Participants information and medical record will be kept in a locked file cabinet in the personal possession of the researcher. Only the researcher and the members of the researchers committee will have the rights to access and review the medical data. Information from this research will be used solely for the purpose of this study and any publications that may result from this study. All participants involved in this study will not be identified and their anonymity will be maintained.

### Recruitment

2.8

There will be 2 primary strategies in recruiting participants with CP. The first strategy is to recruit participants who are patients in the Department of Acupuncture in Jiangsu Province Hospital of TCM and Children^'^s Hospital of Nanjing Medical University. Second, we will post on-line advertisements to briefly introduce our study and recruit patients who are willing to participate.

### Randomization

2.9

Enrolled patients will be randomized into the treatment (acupuncture plus standardized rehabilitation) group or the control (standardized rehabilitation alone) group in a ratio of 1:1, using the “sample” function in R (https://cran.r-project.org/). The randomization code will be placed inside sealed and opaque envelopes that will be opened only after recruitment of the patients.

Criteria of dropout:

1.Participant failed to continue the follow-up due to personal reason or unable to cooperate fully during the assessments.2.Being diagnosed with serious complications or diseases.3.Parents/guardian self-requested for termination of the treatment.

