### Statistical methods

2.14

Normally distributed data will be summarized as means (± standard deviation) and non-normally distributed data as medians (range). The Student t test or the Wilcoxon rank sum test will be used to analyze differences between the groups. If there is heterogeneity of variance, then Satterthwaite corrected *t* test will be used. *P* ≤ .05 will be considered statistically significant and *P* ≤ .0.01 will be considered highly significant.

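### Hospital is a fixed design factor, yet no stratification by hospital is described and the stated between-group tests ignore it; the cost is modest and is largely recovered by adding hospital to the analysis.

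*Protocol article*

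**What the plan says.** Three parts of the protocol article bear on this.

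- **Recruitment** (Participants, section 2.5; also the abstract): "A total of 72 children with CP will be recruited (36 from each of the 2 hospitals) and randomly assigned". Each hospital has a fixed quota.
- **Allocation** (Randomization, section 2.9): children are allocated "in a ratio of 1:1, using the “sample” function in R", with the codes in sealed opaque envelopes. The article mentions no strata, blocks or per-hospital lists. It also does not say that there is a single list or an unrestricted draw.
- **Analysis** (Statistical methods, section 2.14): "The Student t test or the Wilcoxon rank sum test will be used to analyze differences between the groups". For unequal variances it adds: "If there is heterogeneity of variance, then Satterthwaite corrected" t test. None of these tests has a hospital term.

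The Setting section (2.2) says that the study is already under way.

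**The concern.** The plan sets the number of children per hospital in advance, so hospital is a known design factor. As described, neither the allocation nor the analysis then uses it. One site is a Chinese medicine hospital and the other a paediatric hospital. The age range is 6 months to 7 years, and both acupuncture and one-to-one rehabilitation depend on who delivers them. Some difference in outcome level between the sites is plausible.

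Two things would be at stake. If the arms happen to be unbalanced by hospital, part of any hospital difference enters the unadjusted treatment difference. Even with perfect balance, between-hospital variation stays in the error term and costs precision, in a trial of only 72 children.

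**Working it through.** **Inputs.** From the article: 72 children, 36 per hospital, 36 per arm, two-sample tests. Assumed: a difference d in mean outcome between hospitals of 0.5 SD, range 0.3 to 0.8 SD (within-hospital SD = 1), because the article gives none; and a treatment effect of 0.67 SD, chosen because it gives about 80% power at 36 per arm.

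**The plan's own figure.** With "an average efficiency of 92% and 63% for the treatment and the control groups" and "α = 0.05, and β = 0.2" (two-sided assumed), the arcsine formula gives n = (1.960 + 0.842)² / {2 (arcsin√0.92 − arcsin√0.63)²} = 7.85 / {2 (1.284 − 0.917)²} = 29.1, rounded up to the stated 30. Then 30 × 1.2 = 36. The stated size reproduces and does not depend on this point.

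**Step 1: chance of imbalance by hospital, if unstratified.**

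- *One fixed 36/36 list, permuted.* The treated count X at one hospital is hypergeometric (72 children, 36 treated, 36 drawn), with mean 18 and SD 2.14. P(X = 18) = 0.19. P(|X − 18| ≥ 4), a 22:14 split or worse, = 0.098. The other hospital mirrors the split automatically.
- *Each child drawn independently.* X is binomial(36, 0.5) at each hospital. P(|X − 18| ≥ 4) = 0.243 for one hospital, and 1 − (1 − 0.243)² = 0.427 for at least one of the two. These splits need not mirror each other, so what matters is the gap between the arms in the share of children from one hospital. A gap of 20 percentage points or more has probability 0.083.

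**Step 2: effect of an imbalance on the unadjusted difference.** With a mirrored 22:14 split the shift is d × (22/36 − 14/36) = 0.222d.

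| Assumed d | Shift |
|---|---|
| 0.3 SD | 0.07 SD |
| 0.5 SD | 0.11 SD |
| 0.8 SD | 0.18 SD |

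If only one hospital splits 22:14 and the other is 18:18, the shift is d × (22/40 − 14/32) = 0.1125d, or 0.056 SD at d = 0.5. If both split 22:14 in the same direction, it is zero.

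**Step 3: precision.** With equal hospital sizes, ignoring hospital multiplies the outcome variance by about 1 + d²/4: 1.02, 1.06 and 1.16 at d = 0.3, 0.5 and 0.8. Approximate power of the unadjusted test is Φ(0.67 / √{(1 + d²/4) × 2/36} − 1.994):

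- d = 0: Φ(2.843 − 1.994) = 0.80
- d = 0.5: Φ(2.758 − 1.994) = 0.78
- d = 0.8: Φ(2.639 − 1.994) = 0.74

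Simulation agrees: about 0.80, 0.77-0.78 and 0.73-0.74. With a hospital term, simulated power stays at about 0.79 to 0.80 throughout. Type I error of the unadjusted test after unstratified allocation stays near 5% (0.046 to 0.053 across the simulated cases).

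**Step 4: if allocation was in fact stratified, 18:18 in each hospital.** The imbalance is zero, but the unadjusted t test still counts hospital variation as error and becomes conservative. Simulated type I error is about 0.044 to 0.046 at d = 0.5, 0.035 at 0.8 and 0.028 at 1.0. With hospital in the model it is about 0.05, and power is about 0.80 to 0.81.

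**The case against.** **Silence is not a statement.** A reader might infer that randomisation is unstratified, or that one unrestricted draw was made. The Randomization section says neither. `sample` can be run separately by hospital, within blocks, or as a permutation of a fixed list, and a condensed article commonly leaves such detail to the full protocol. This objection stands for the allocation half: only the absence of a description can be asserted. It does not dispose of the analysis half, because the Statistical methods section names the tests, and Step 4 shows that stratified allocation would still call for a hospital term.

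**It is not bias in the usual sense.** A reader might infer that the treatment estimate is biased. It is not, on average over the randomisation, and the test's error rate already allows for chance imbalance. The 0.11 SD shift is conditional on a poor split.

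**The larger probabilities do not belong with the larger shift.** A reader might pair the 43% chance of a 22:14 or worse split at one or other hospital with the 0.11 SD shift. The 43% arises from independent draws, where mirroring is not guaranteed. The matching probability there is about 8%, close to the 10% for a fixed list.

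**Site differences are partly contained.** The Discussion has a single department interpret the MRI and EEG recordings, two of the three primary outcomes. Eligibility criteria are common, and rehabilitation is described as standardised. This limits differences in reading for those two outcomes. It does not remove differences in case mix or in delivery of treatment.

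**Conclusion.** The point holds in limited form. Hospital is fixed by design, no stratification by hospital is described, and the stated tests leave hospital out. The analysis part is a stated choice for which a better method is available; the allocation part is a matter to clarify.

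The size is modest. It is about a 10% chance of a split that would shift the unadjusted difference by at least 0.11 SD at an assumed 0.5 SD hospital difference (0.07 to 0.18 SD over the assumed range), and a power loss of 2 to 3 percentage points at 0.5 SD and 6 to 7 points at 0.8 SD. If the hospitals do not differ, nothing material is lost. The document does not support a claim that the comparison is invalid or its type I error inflated.

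**What to change.** **Analysis (main change).** Before results are seen, replace the two-sample tests as the main between-group analysis with one that includes hospital, for all children randomised. Examples are a linear model with treatment and hospital, or a hospital-stratified van Elteren test for non-normal outcomes. The two-sample tests can remain as a sensitivity analysis. This uses data already held, works however the allocation was made, and costs one model term and a short amendment.

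**Allocation (secondary).** State whether the lists are separate by hospital. If they are, one sentence settles it. If not, use per-hospital permuted-block lists with randomly varying block sizes, and a separate envelope series for each hospital, for children not yet randomised. The cost is a few lines of R code, a second envelope series and inclusion in the same amendment. The small downside is that blocks are slightly predictable in an open-label trial, which random block sizes limit. Because the study is under way, this can help only the remaining children.

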### Case dropout management:

2.10

Participants have a right to withdraw from the study at any time if they feel uncomfortable upon receiving the treatments or being diagnosed with serious complications or diseases. They will then be referred to the preferred department for further treatment and management. If cases of dropout, the researcher need to contact the participant to reason the problem out, collect, and record all the necessary assessments on the last visit as well as the date of last visit. All data available until the date of withdrawal will be stored for further statistical analysis.

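### The drop-out criteria treat a failed assessment, a serious complication and a stopped treatment as leaving the study, and no 3- or 6-month outcome collection is described afterwards

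*Protocol article*

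**What the plan says.** Section 2.9 (Randomization) of the protocol article gives three drop-out criteria:

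1. "Participant failed to continue the follow-up due to personal reason or unable to cooperate fully during the assessments"
2. "Being diagnosed with serious complications or diseases"
3. "Parents/guardian self-requested for termination of the treatment"

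Section 2.10 (Case dropout management) adds that families may withdraw "if they feel uncomfortable upon receiving the treatments or being diagnosed with serious complications or diseases". When a child drops out, the researcher contacts the family and is to "record all the necessary assessments on the last visit as well as the date of last visit". It closes with "All data available until the date of withdrawal will be stored for further statistical analysis". Section 2.6 (Informed consent) says that, for a patient who withdraws, "all data available till the date of withdrawal will be included in the final analysis".

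Section 2.13 sets the outcome times at baseline, 3 months and 6 months after the start of treatment. Section 2.12 gives acupuncture to one arm only, with rehabilitation alone and no sham in the other. Section 2.4 allows for 20% loss.

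**The concern.** Only the first half of criterion 1 is loss to follow-up in the usual sense. The second half is a measurement problem, criterion 2 is a clinical event, and criterion 3 is the end of treatment. In principle, a child in any of the last three situations can still be assessed at 3 and 6 months. By calling all of them drop-outs and describing data only up to withdrawal, the article gives up outcomes that could have been collected.

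This matters because these events need not be random. Discomfort from treatment, a complication, or a parent's wish to stop may depend on which treatment the child receives and on how the child is doing. If the children without later outcomes differ from the rest, and differ in number or kind between arms, those left with a 3- or 6-month value are no longer the groups that were randomised. No later analysis can recover outcomes that were never measured, so this cannot be left to an analysis plan.

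**Working it through.** **Step 1. What each criterion describes, and whether outcomes remain obtainable**

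| Criterion (section 2.9) | What has happened | Can 3- and 6-month outcomes still be collected? | What sections 2.6 and 2.10 provide |
|---|---|---|---|
| 1, first half | Family leaves follow-up | Often not | Last-visit assessment, data to withdrawal |
| 1, second half | Child cannot cooperate fully with assessments | Possibly, on the other measures | Same |
| 2 | Serious complication or disease | Often yes | Same |
| 3 | Parents ask to end treatment | Usually yes | Same |

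The third column is a judgement; the others come from the article. Nothing in the article describes a 3- or 6-month assessment once a criterion is met.

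**Step 2. The cooperation wording**

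Criterion 1 does not say which assessments, or how many, must fail. The strengths and limitations list at the end of the abstract says of MRI, a primary outcome: "The results of MRI might vary or be unclear because children are unlikely to cooperate during the examination". Read literally, a failed MRI could therefore make a child a drop-out on the Gesell schedules, GMFM and WeeFIM as well. A narrower reading, that the child cannot be assessed at all, is also possible. The text does not decide between them.

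**Step 3. The plan's own figures**

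Inputs from section 2.4: 92% versus 63%, α = 0.05, β = 0.2, 20% loss.

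- The arcsine formula, two-sided, n = 2(1.960 + 0.842)² / (2·arcsin√0.92 − 2·arcsin√0.63)², gives 29.1, so 30 per group, as stated. The pooled two-sided formula gives 32.
- Loss allowance: 30 × 1.2 = 36 per group, as stated.
- Children left after 20% loss: 36 × 0.8 = 28.8 per group. Power (two-sided, pooled) is about 76%, against about 85% if all 36 are kept. Outcomes that need not be lost therefore also cost power.

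**Step 4. Illustration of bias (assumed inputs)**

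The article gives neither loss by arm nor outcome among drop-outs, so both are assumed. The response scale is used because section 2.4 gives figures only on that scale. Assume no true effect, with 63% response in both arms, and a comparison of children who have the later outcome. With loss share d and response q among drop-outs, the completer response is (0.63 − d·q)/(1 − d).

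| Loss, acupuncture / control | q | Completer rates | Spurious difference | Type I error |
|---|---|---|---|---|
| 20% / 20% | 0% | 0.63/0.8 = 78.7% in both | 0 | about 5% |
| 20% / 10% | 0% | 0.63/0.8 = 78.7%; 0.63/0.9 = 70.0% | 9 points | 12% |
| 20% / 10% | 30% | 0.57/0.8 = 71.3%; 0.60/0.9 = 66.7% | 5 points | 7% |
| 30% / 10% | 0% | 0.63/0.7 = 90.0%; 70.0% | 20 points | 46% |
| 30% / 10% | 30% | 0.54/0.7 = 77.1%; 66.7% | 10 points | 14% |
| any split | 63% | 63% in both | 0 | about 5% |

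Type I error comes from a simulation with 36 per arm, 200,000 runs and a pooled z-test at the two-sided 5% level. Swapping the loss shares between arms reverses the sign of the difference.

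**The case against.** The strongest reply is that the article keeps all data up to withdrawal, asks for a last-visit assessment, and nowhere forbids later visits; a condensed article may leave such procedures to the full protocol. Part of this stands: drop-outs are not deleted, and the absence of later visits is something the article does not describe rather than something it prohibits. But the article does state the definition and the data cut, and as stated they put stopping treatment on the same footing as leaving the study.

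Several stronger readings are tempting and are not supported:

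- **One failed MRI removes a child from every scale.** The criterion speaks of assessments in the plural and sits beside failure to continue follow-up. The limitations list describes poor MRI data, not withdrawal. The cascade is a possible literal reading, not a stated rule.
- **Early last-visit values will stand in for 3- or 6-month outcomes.** Section 2.6 says available data are included; it does not say they are carried forward.
- **The EEG text shows that the same failure is expected there.** Section 2.13.1.2 attributes poor cooperation to conventional EEG and offers ambulatory EEG, the trial's outcome, as the alternative.
- **The bias must favour acupuncture.** Disappointed control families could leave instead. The cooperation criterion applies to both arms, which have the same assessments, and equally informative loss in both cancels.
- **Loss is strongly tied to severity.** Section 2.5 excludes severe spastic cerebral palsy, which narrows that link without removing it.

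The illustration also assumes a comparison of children with the later outcome, which the article does not specify.

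**Conclusion.** The point holds as a flaw in a stated rule. Section 2.9 joins a measurement failure, a clinical event and the end of treatment to true loss to follow-up, and sections 2.6 and 2.10 describe no outcome collection afterwards. With needling in one arm only and no sham, loss under criteria 2 and 3 can plausibly differ by arm and relate to outcome.

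Neither the size nor the direction of any bias can be fixed from the article. The illustrated range runs from zero (equally informative loss, or drop-outs who respond like the rest) to 20 points (30% versus 10% loss with no drop-out responding), and every loss split and drop-out response in it is an assumption. What is certain is that outcomes which could be collected may not be. The change should be made, and confidence in its practical importance is moderate.

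**What to change.** Reword the criteria in section 2.9, and align sections 2.6 and 2.10 with them, so that:

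- (a) a failed or refused assessment makes only that measurement missing, and the child stays in the study for all others;
- (b) stopping treatment, or a serious complication or disease, does not end outcome follow-up. The 3- and 6-month assessments already scheduled are still collected, and the child is kept in the assigned arm, unless the parent withdraws consent for data collection.

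The rules for when treatment stops are not touched. The cost is amendment wording and some attended visits by families who have stopped treatment. Scales scored on the child's performance, such as GMFM, need attendance, so telephone contact alone will not supply them. The visits are already in the schedule, so no new procedure is added.
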